### 933 **IX.3. Main analysis**

934 The analysis of the main objective, i.e. the rate of severe toxicity of grade  $\geq 3$  to 2 years, with its 95%  
 935 CI will be compared to 15% (with regard to the assumptions set in the context of the estimation of  
 936 the number of subjects needed). If the 95% CI does not include this rate, the trial will be considered  
 937 positive. For efficacy endpoints, 95% bilateral confidence intervals will be provided. Statistical  
 938 analysis will be performed on an intention-to-treat basis.

939 An analysis of the predictive factors of severe toxicity of grade  $\geq 3$  to 2 years will be performed. A  
 940 univariate analysis will be performed using the usual tests: Student's test or Mann-Whitney test if the  
 941 conditions of the t-test are not met (normality, and homoscedasticity studied by the Fisher-Snedecor  
 942 test) for quantitative variables and Chi2 test or Fisher's exact test for categorical variables. The  
 943 multivariate analysis will consider a logistic regression model for binary dependent variable.  
 944 Covariates will be retained based on the results of univariate analysis and their clinical relevance.

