### IX.1. Number of topics to include

881 To determine the number of patients needed, two objectives were considered: severe late toxicity at  
882 2 years (primary outcome) and local control rate at 2 years (secondary outcome). The experimental  
883 design follows a one-step Fleming design with no intermediate analysis due to the primary endpoint  
884 which will be evaluated at 2 years (severe late toxicity).

885 The safety and efficacy profile of hypofractionated stereotactic radiotherapy of the operative bed is  
886 expected to be equivalent to other radiotherapy techniques (brachytherapy or normofractionated  
887 IMRT) (cf 3. Rationale of the study for details). In brachytherapy, the rate of late soft tissue ulceration  
888 is around 10-20% and the rate of bone necrosis is around 5-10%. We have decided: 1/ to accept a rate  
889 of less than 5% and 2/ to reject a rate of more than 15%. With a unilateral test for significance ( $\alpha=0.05$ )  
890 with a power of 90% ( $\beta=0.10$ ), the minimum number of patients to be included is 67.  
891 Hypofractionated stereotactic radiotherapy of the operative bed will then be considered an  
892 unacceptable treatment if 6/67 patients (9%) or more have severe late toxicity (grade  $\geq 3$ ).

893 The local control rate of hypofractionated stereotactic radiotherapy is expected to be equivalent to  
894 other radiotherapy techniques (brachytherapy or normofractionated IMRT). We have decided: (i) to  
895 accept a rate of more than 90% and (ii) to reject a rate of less than 80%. With a one-sided significance  
896 test ( $\alpha=0.05$ ) with a power of 80% ( $\beta=0.20$ ), the minimum number of patients to be included is 83.  
897 A lower potency was decided for control as a secondary outcome. Hypofractionated stereotactic  
898 radiotherapy of the operative bed will then be considered an acceptable treatment if 72/83 patients  
899 (87%) or more are locally controlled at 2 years.

900 As a result of these results, and to compensate for possible loss to follow-up, a total of 90 patients  
901 will be included in this study.

902 As the primary objective of this study is estimated at 2 years, once 30 patients have been included  
903 (33% of inclusions), a review of all grade  $\geq 3$  toxicities will be communicated to the independent trial  
904 monitoring committee (IDSMC = *Independent Data and Safety Monitoring Committee*). The grade 4  

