### 906 IX.2. Data analysis: general

907 Patients will be described and compared between groups at baseline according to the following  
908 variables:

- 909 • Compliance with eligibility criteria
- 910 • Epidemiological characteristics
- 911 • Clinical and treatment characteristics.

912 A description of the deviations from the protocol, the patients distributed according to these  
 913 deviations and the causes of abandonment will also be carried out. The number of patients included  
 914 and the curve of inclusions will be presented by groups.

915 Continuous variables will be presented as a mean and standard deviation, subject to the normality of  
 916 their distribution (Shapiro-Wilk test if necessary). In case of non-normality, they will be presented in  
 917 the form of median, quartiles and extreme values. The qualitative variables will be expressed in terms  
 918 of numbers and associated percentages. 95% confidence intervals (95% CI) will be reported. For each  
 919 variable, the number of missing data will be specified. Graphical representations will be associated  
 920 with these analyses as much as possible.

921 The estimate of the theoretical follow-up time will be the time difference between the date of inclusion  
 922 and the date of the database freeze. The follow-up will also be estimated according to the reverse  
 923 Kaplan Meier method for the observed follow-up. The parameters related to the time to events (SSR,  
 924 OS...) as well as the time to deterioration of quality of life (scores) will be estimated according to the  
 925 Kaplan-Meier method and described with a median confidence interval and rates at defined periods.  
 926 Patients without specific events at the time of study termination (baseline freeze of study data) will  
 927 be censored, for the "time to events" criteria, as of the date of the last update. Possible comparisons  
 928 between independent groups will consider the log-rank test (univariate analysis) and the Cox model  
 929 (multivariate analysis).

930 Tests will be bilateral, and a  $p < 0.05$  value will be considered statistically significant. As this trial  
 931 is exploratory, the adjustment of the risk of error of the first kind will not be proposed systematically,  
 932 but on a case-by-case basis in view of clinical and not only statistical considerations (48).

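### Sections IX.1 and IX.3 give two different decision rules for the primary toxicity endpoint, and they can disagree on the same data

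*Protocol*

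**What the plan says.** Three places in the protocol bear on how the primary endpoint is decided.

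- **IX.1 (sample size).** The "design follows a one-step Fleming design with no intermediate analysis". The acceptable and unacceptable rates are set as "of less than 5% and 2/ to reject a rate of more than 15"%. The sizing is done "With a unilateral test for significance" at 0.05 and "with a power of 90"%, which gives a minimum of 67. The decision rule is a count: the procedure is an "unacceptable treatment if 6/67 patients (9%) or more have severe late toxicity". Local control needs 83 patients, and 90 are enrolled to allow for loss to follow-up.
- **IX.2 (general analysis).** "Tests will be bilateral", with significance at p<0.05 and no exception for the primary test.
- **IX.3 (main analysis).** The severe toxicity rate and its 95% CI are compared with 15%. "If the 95% CI does not include this rate, the trial will be considered" positive. The analysis is by intention to treat. The 6/67 cut-off is not mentioned, and no toxicity cut-off is given for 83 or 90 patients.

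**The concern.** A single-arm trial with one primary endpoint should have one decision rule. Here one section uses a count cut-off built on a one-sided 5% error, and another uses a 95% confidence interval, which on the usual reading spends 2.5% on each side. If the two can give different answers, the primary conclusion depends on which section is followed. The power quoted for one rule also need not belong to the other.

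Two further gaps make the IX.3 rule hard to apply. It does not say on which side of 15% the interval must lie. The only count in the protocol is for 67 patients, although 90 are enrolled.

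**Working it through.** **Inputs.** From IX.1: rates 5% and 15%, one-sided alpha 0.05, power 90%, cut-off 6/67, minimum 83 for local control, 90 enrolled. From IX.3: 95% CI against 15%. The interval method is not stated, so several are tried. The number analysed is not known in advance, so 67, 83 and 90 are shown.

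**1. The plan's own sample size.** The single-proportion normal approximation is

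n = [(z_α √(p0 q0) + z_β √(p1 q1)) / (p1 − p0)]², with z_α = 1.645 and z_β = 1.282.

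With p0 = 0.05 and p1 = 0.15, n = 66.6, so 67. The stated figure is reproduced. It takes 5% as the null, whereas IX.3 tests against 15%. With 15% as the null the same formula gives 75.1, so 76, which is still below the 90 enrolled.

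**2. Properties of the IX.1 rule.** The treatment is not unacceptable with at most 5 events in 67. By exact binomial:

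- P(X ≤ 5 | n=67, 5%) = 88.2%
- P(X ≤ 5 | n=67, 15%) = 5.1%

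The count rule itself is therefore slightly under the stated 90%.

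**3. The same data under IX.3.** Two-sided 95% intervals for 5/67 (7.5%):

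- exact (Clopper-Pearson): 2.5% to 16.6%
- Wilson: 3.2% to 16.3%
- Wald: 1.2% to 13.8%

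The exact and Wilson intervals include 15%, so 5/67 is not positive under IX.3 although it is not unacceptable under IX.1. Of the methods tried, only Wald makes the two rules agree at n=67.

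**4. Properties of the IX.3 rule, read as a two-sided 95% upper limit below 15%.** Each cell gives the largest count that passes, the power at 5% and the error at 15%.

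| Method | n=67 | n=83 | n=90 |
|---|---|---|---|
| Exact | 4; 75.7%; 2.0% | 5; 76.5%; 1.0% | 6; 83.6%; 1.3% |
| Wilson | 4; 75.7%; 2.0% | 6; 87.8%; 2.6% | 6; 83.6%; 1.3% |
| Agresti-Coull | 4; 75.7%; 2.0% | 5; 76.5%; 1.0% | 6; 83.6%; 1.3% |
| Jeffreys | 4; 75.7%; 2.0% | 6; 87.8%; 2.6% | 7; 91.9%; 3.1% |
| Wald | 5; 88.2%; 5.1% | 7; 94.4%; 5.7% | 8; 96.4%; 6.3% |

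At n=90 the result for 7 or 8 events turns on the method. For 7/90 the exact interval is 3.2% to 15.4% (not positive) and the Wald upper limit is 13.3% (positive).

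**5. Direction.** The exact 95% CI lies wholly above 15% from 21/90 (23.3%; lower limit 15.06%) or 17/67 (25.4%). Such an interval also does not contain 15%, so the sentence in IX.3, taken alone, would be met.

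**6. A single exact one-sided rule.** Require the exact one-sided 95% upper bound (the upper limit of the two-sided 90% CI) to be below 15%.

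| n analysed | Positive if at most | Power at 5% | Error at 15% |
|---|---|---|---|
| 83 | 6 | 87.8% | 2.6% |
| 84 | 6 | 87.3% | 2.4% |
| 85 | 7 | 93.8% | 4.8% |
| 90 | 7 | 91.9% | 3.1% |

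For 5/67 this bound is 15.05%, so 5/67 fails this rule too.

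**The case against.** **A one-sided reading is available.** The toxicity sentence in IX.3 says only 95% CI; the word bilateral appears in the next sentence, for efficacy endpoints. The statement in IX.2 is general and follows the group comparisons. This stands in part: two-sided is the natural reading, not an explicit one. It does not remove the conflict, because the exact one-sided bound for 5/67 is still above 15%.

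**The interval method can be left to the analysis plan.** This stands. A reader might infer that the trial has certainly lost its 90% power. The protocol does not support that: at n=90, Jeffreys and Wald intervals keep at least 90%, and Wald reconciles the two sections at n=67. The 75.7% figure belongs to n=67, while 90 are enrolled. The analysis plan cannot, however, resolve two different rules in the protocol without departing from one of them.

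**Direction.** A reader might also infer that the plan would declare a clearly too toxic treatment a success. The documents do not support that as the intended rule. IX.3 ties its comparison to the sizing assumptions, and IX.1 accepts low rates and rejects high ones. What remains is an incomplete sentence in the criterion for success.

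**A stricter interval is a legitimate choice.** This also stands. Keeping the two-sided rule would be acceptable if its power were restated.

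**Conclusion.** The point holds as an unreconciled pair of decision rules for the primary endpoint. On the two-sided reading, 5/67 gets different answers under IX.1 and IX.3 with every interval method tried except Wald. With an exact interval, power at a true 5% rate is 75.7%, 76.5% and 83.6% at 67, 83 and 90 patients, against the stated 90% and the 88.2% that the IX.1 rule delivers. The size of the loss is conditional on the interval method and on the number analysed, and at n=90 it disappears with Jeffreys or Wald. The Wald rule pays for this with a 6.3% error at 15%.

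The missing direction is a drafting gap whose intent is clear. The missing cut-off for the enrolled number is real: at 90 patients the protocol gives no count, and the verdict on 7 or 8 events depends on an unstated choice. This should be settled before the data are analysed, because it determines the primary conclusion.

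**What to change.** State one directional rule, in the same words, in IX.1 and IX.3: the trial is positive if the exact (Clopper-Pearson) one-sided 95% upper bound for the severe late toxicity rate, which is the upper limit of the two-sided 90% CI, is below 15%.

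- Replace the 6/67 cut-off, since 5/67 does not meet this rule, with a table by number analysed, such as the one in step 6 of the working.
- Say that power is slightly under 90% at some analysed numbers (87.8% at 83, 87.3% at 84).
- Keep the two-sided 95% CI as a description only, and exempt the primary test from the general statement on two-sided tests in IX.2.

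Alternatively, keep the two-sided 95% CI as the rule, name the exact method, add that the upper limit must be below 15%, give the matching cut-offs, and restate the power as 83.6% at n=90.

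Either option changes wording only, in the protocol and the analysis plan, and needs no extra patients.

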## STATISTICAL CONSIDERATIONS

### Estimating the number of patients needed

With a one-step Fleming plan, the calculation of the number of patients needed takes into account:

- The primary endpoint: severe toxicity at 2 years limited to 5-15%, minimum N is equal to 67 patients (unilateral,  $\alpha = 0.05$ ,  $\beta=0.10$ )
- and the secondary endpoint: 2-year local control of 80-90%, minimum N is equal to 83 patients (unilateral,  $\alpha = 0.05$ ,  $\beta=0.20$ )

In order to compensate for possible loss to follow-up, 90 patients will be included.

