### IV. RESEARCH DESIGN

#### IV.1. Primary endpoint

**Rate of patients with late toxicity at 2 years grade  $\geq 3$**  according to the NCI - CTCAE V4.03 classification in connection with hypofractionated stereotactic radiotherapy, i.e. grade  $\geq 3$  toxicities occurring beyond 3 months after the end of stereotactic radiotherapy.

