### 430 **V.3. Description of stop rules**

431 *V.3.1 Permanent or temporary cessation of a person's participation*

432 All patients included in this study will have the right to leave the study at any time, without having  
433 to justify the reason and without this calling into question their usual medical follow-up.

434 The reasons for leaving the study must be related to the following criteria:

- 435 • Withdrawal of consent: the patient will be free to stop the study at any time and without  
436 prejudice to his or her further treatment. The patient will have to specify whether he or she  
437 only wishes to stop the current treatment, or whether he or she also wishes to stop the  
438 monitoring provided for in the protocol or whether he or she wishes to have the data already  
439 collected in the database about him or her destroyed.
- 440 • Unacceptable toxicity attributed to treatment
  - 441 • Pregnancy
  - 442 • Non-compliance with the protocol
  - 443 • Patient lost to follow-up
  - 444 • Death.

445 *V.3.2 Premature discontinuation of study treatment*

446 Treatment may be discontinued prematurely for the following reasons:

- 447       • Toxicity
- 448       • Disease progression
- 449       • Refusal to continue the trial, withdrawal of consent

- Major breach of protocol.

Whenever possible, patients who have discontinued treatment prematurely will be monitored according to the protocol.

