## VI.2. Recruitment procedures

Patients will be screened in a Multidisciplinary Consultation Meeting (RCP) and those who are potentially eligible for the study (indication of irradiation of the operating bed) will be seen in consultation by a radiotherapist and/or a surgeon, who will offer them to participate in the trial. Patients who meet the inclusion criteria without non-inclusion criteria, and who have signed informed consent will be eligible to participate in this trial. Inclusion is done via the electronic CRF and must be performed before the start of stereotactic radiotherapy. The included patients will be treated according to the modalities provided for in the trial.

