1032 from the SAE reporting procedure, namely:

- 1033 ❖ Scheduled hospitalization prior to the start of the trial
- 1034 ❖ Hospitalization or surgery related to the treatment of the disease
- 1035 ❖ Any event occurring between the signing of the consent and the performance of

stereotactic radiotherapy

- ❖ Deaths related to disease progression.

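### Intention to treat is stated for the primary toxicity analysis, so any included patient who is never irradiated can only dilute the rate compared with 15%; the effect is probably small.

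*Protocol*

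**What the plan says.** Protocol IX.3 (Main analysis) sets the primary comparison: the rate of grade 3 or higher toxicity at 2 years, with its 95% confidence interval, is compared with 15%, and the trial is positive if the interval excludes 15%. After a sentence on intervals for efficacy endpoints, the paragraph ends by saying that "analysis will be performed on an intention-to-treat basis". No treated or safety population is named there or elsewhere in section IX.

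Three other places matter:

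- **IV.1 (Primary endpoint)** counts toxicity connected with the stereotactic radiotherapy, namely "toxicities occurring beyond 3 months after the end of stereotactic radiotherapy".
- **VI.2 (Recruitment procedures)** says that inclusion "must be performed before the start of stereotactic radiotherapy".
- **V.3.1** lists as a reason for leaving the study: "Withdrawal of consent: the patient will be free to stop the study at any time". XI.1.2 recognises the interval before treatment, because it removes from serious-event reporting "Any event occurring between the signing of the consent and the performance of" the radiotherapy.

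IX.1 justifies the step up to 90 patients by loss to follow-up and mentions no allowance for untreated patients. IX.5 covers missing data in general terms, leaves the imputation method open, and does not mention patients who were never irradiated.

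**The concern.** Intention to treat is usually the cautious choice because it guards against selective exclusion in a randomised efficacy comparison. This trial has one arm, and its primary endpoint is a harm tested against a ceiling. A patient who is included but never irradiated cannot have a toxicity linked to radiotherapy more than 3 months after its end. Such a patient can enlarge the denominator but cannot add to the numerator.

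The direction of the bias is therefore fixed: the estimated rate falls and a treatment with an unacceptable rate passes more easily. The main objective (II.1) asks for the late toxicity of the radiotherapy itself, so the rate among irradiated patients is the quantity of interest. If the population is left unsettled, the denominator could also be chosen after the data are seen, when the result lies near the boundary.

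**Working it through.** **Inputs from the protocol.** Rates of 5% (acceptable) and 15% (unacceptable), the unacceptable-if-6-of-67 rule, and 90 patients (IX.1); positive if the 95% interval excludes 15% (IX.3).

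**Assumptions.** The number never irradiated, u, is not given; 3 to 7 of 90 is used. The protocol names no interval method, so exact (Clopper-Pearson) limits are used. Never-irradiated patients are counted as non-events.

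**Reproducing the plan's figure.** The synopsis gives "severe toxicity at 2 years limited to 5-15%, minimum N is equal to 67 patients". IX.1 adds the error rates: "With a unilateral test for significance" at 0.05, "with a power of 90"%. The one-stage normal-approximation formula is

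n = [(z₀.₉₅·√(p₀q₀) + z₀.₉₀·√(p₁q₁)) / (p₁ − p₀)]²

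With p₀ = 0.05 and p₁ = 0.15: n = [(1.645 × 0.2179 + 1.282 × 0.3571) / 0.10]² = 66.6, so 67. The stated figure reproduces.

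**Step 1: dilution.** If the true rate in irradiated patients is 15%, the expected intention-to-treat rate is 15% × (90 − u)/90.

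- u = 3: 15% × 87/90 = 14.5%
- u = 5: 15% × 85/90 = 14.2%
- u = 7: 15% × 83/90 = 13.8%

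**Step 2: the cut-off under IX.3.** With 90 in the denominator, 6 events pass (upper limit 13.9%) and 7 do not (upper limit 15.4%). The trial is positive with 6 or fewer events.

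**Step 3: chance of a positive trial at a true 15%.** Only 90 − u patients can have an event, so the chance is P(X ≤ 6) with X binomial(90 − u, 0.15).

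| Never irradiated | At risk | P(X ≤ 6) |
|---|---|---|
| 0 | 90 | 1.3% |
| 3 | 87 | 1.8% |
| 5 | 85 | 2.2% |
| 7 | 83 | 2.6% |

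**Step 4: does the verdict change with a treated denominator?** The upper limit for 6 events is 14.7% with 85 treated, 14.9% with 84 and 15.07% with 83. The cut-off therefore stays at 6 events with up to 6 untreated and drops to 5 at 7 untreated. There, 6 events pass as 6/90 but not as 6/83. With the cut-off of 5, the chance of a positive trial at a true 15% is 1.0% instead of 2.6%.

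**Step 5: the 6/67 rule of IX.1.** Acceptance means 5 or fewer events. At a true 15%, P(X ≤ 5) is 5.1% with all 67 irradiated and 8.1% if 5 of the 67 are not (62 at risk).

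**The case against.** Several points count against a stronger reading.

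- **Scoring.** A reader might infer that the protocol declares untreated patients toxicity-free. It does not. Intention to treat says who is analysed, not how an unobserved outcome is scored. IX.5 leaves imputation open and lists a maximum-bias option, under which such patients could even count as events. V.3.1 also lets a withdrawing patient have collected data destroyed. This stands: non-event scoring is the natural result of combining intention to treat with the endpoint definition, but it is an inference.
- **Scope.** The sentence follows one on efficacy endpoints and might be meant only for them. But it carries no such limit and closes the paragraph that defines the primary comparison. An analysis plan could define a treated set, but it would then have to be reconciled with this sentence.
- **How patients could go untreated.** A reader might cite the Table 4 dose limits as a bar to treatment. They are planning objectives, and VIII.2.1 provides for recording deviations, so they do not support the point. What remains is withdrawal or a change in the patient's condition in a short interval, after the indication has already been agreed.
- **Size.** A reader might conclude that the primary result is unsafe. The figures do not show this. With up to 6 untreated, the exact cut-off does not move. Even 2.6% is well below both error rates in IX.1 (5% and 10%), though it just exceeds the 2.5% per tail of a two-sided 95% interval. With Wilson limits, 6/83 would still pass (upper limit 14.9%). Seven events cannot be used to enlarge the effect, because 7/90 fails the two-sided rule.
- **Remedy.** Restricting to treated patients does not deal with those who die or recur early. VI.5.3 limits follow-up after recurrence to vital status, so their late toxicity is not collected. This is true, but it is a separate source of dilution and no reason to keep the first.

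**Conclusion.** The point holds. IX.3 as written applies intention to treat to a single-arm toxicity endpoint without restriction, and any never-irradiated patient kept as a non-event biases the rate toward acceptance. The direction does not depend on how many there are; the size does, and the protocol gives no count.

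At the assumed 3 to 7 of 90, the bias is about 0.5 to 1.2 percentage points on a true 15%. The false-acceptance chance under the interval rule rises by 0.5 to 1.3 percentage points, and a verdict changes only at exactly 6 events with 7 untreated. The effect is larger under the 6/67 rule, at 3.0 percentage points for 5 untreated of 67 (5.1% to 8.1%), but remains below the 10% implied by the stated power. These figures rest on the assumed counts, on non-event scoring and, for the interval rule, on exact limits. This is a flaw worth correcting because the correction is nearly free, not one that invalidates the design.

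**What to change.** In IX.3, state that the primary toxicity rate is analysed in all patients who received at least one fraction of stereotactic radiotherapy. Limit the intention-to-treat sentence to local control, locoregional control, recurrence-free survival and overall survival. Report the number included but never irradiated, with reasons, so that the difference between the two denominators is visible.

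The cost is one sentence, and the toxicity denominator may shrink by a few patients. At 83 treated, the cut-off falls from 6 events to 5, and the chance of a positive trial at a true 5% is 76.5% rather than the 87.9% obtained by keeping 90 in the denominator. No change to treatment or follow-up is involved.

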#### IV.2. Secondary endpoints

- **Local control at 2 years.** Will be considered as an event: local recurrence (T) documented in the area of the operating bed. The diagnosis of local recurrence requires histological confirmation.
- **Locoregional control at 2 years.** The following are considered to be events: local recurrence (T) and/or lymph node recurrence (N), i.e. ipsilateral or contralateral cervical positive lymphadenopathy(es). The diagnosis of regional recurrence requires confirmation by imaging and/or histologic.
- **Grade  $\geq 3$  acute toxicity** (toxicities occurring during treatment up to  $\leq 3$  months after the end of treatment) in connection with hypofractionated stereotactic radiotherapy, according to the NCI classification - CTCAE V4.03
- **2-year recurrence-free survival (RSS):** defined as the time interval between the date of inclusion and the date of the first cancer event (local recurrence, regional recurrence, distant metastasis) or death from any cause.

- 385 • **2-year overall survival (OS):** defined as the time interval between the date of inclusion and
- 386 the date of death from any cause.
- 387 • **Quality of Life (QoL):** according to the EORTC QLQ-C30 and EORTC-H&N35
- 388 questionnaires
- 389 • **Nutritional impact,** assessed by patient weight and feeding tube use.
- 390 • **Predictive factors of toxicity at 2 years :** clinical and/or dosimetric factors associated with
- 391 late severe toxicity.

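### Predictors of severe late toxicity are to be selected on univariate results with roughly 4 to 8 events, so the retained odds ratios will be overstated

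*Protocol*

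**What the plan says.** Identifying predictors of toxicity is a secondary objective (Protocol, Synopsis and II.2). Section IV.2 makes it an endpoint: "clinical and/or dosimetric factors associated with" severe late toxicity. The number of candidate factors is not given.

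Section IX.3 sets the method in two steps. First come univariate tests (Student or Mann-Whitney for quantitative factors, Chi2 or Fisher for categorical ones). Then the "multivariate analysis will consider a logistic regression model for binary dependent variable". The link between the steps is explicit: "Covariates will be retained based on the results of univariate analysis and their clinical relevance". The section states no entry threshold, no limit on the number of covariates and no penalised or exact method.

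The protocol states no expected number of events, but IX.1 supplies what is needed to derive it. The design accepts a rate "of less than 5% and 2/ to reject a rate of more than 15"%, includes 90 patients, and calls the treatment an "unacceptable treatment if 6/67 patients (9%) or more have severe late toxicity". Section IX.3 adds that the trial is positive if the 95% confidence interval for the rate excludes 15%.

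**The concern.** Two problems arise when a logistic model is built on a handful of events.

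The first is selection. A factor passes a univariate screen on few events only if its observed association happens to be large. Estimates that survive are therefore biased away from the null, and the later multivariable fit on the same patients does not undo this.

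The second is separation. When all events fall on one side of some combination of covariates, the maximum-likelihood odds ratio is infinite.

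At stake is the credibility of whatever predictors the trial reports. The event count is lowest when the treatment is safe, so the analysis is least reliable when the trial succeeds.

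**Working it through.** **Inputs from the protocol.** IX.1: 5% accepted, 15% rejected, one-sided α 0.05, power 90%, minimum 67 for toxicity and 83 for local control, 90 included, cut-off 6/67. IX.3: 95% CI must exclude 15%.

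**The plan's own figure.** n = [(1.645·√(0.05·0.95) + 1.282·√(0.15·0.85)) / 0.10]² = [(0.358 + 0.458)/0.10]² = 66.6, so 67, as stated (with 5% taken as the null). The sample size was built for a single proportion, not for a regression.

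**Expected events (N × rate).**

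| Rate | N=67 | N=83 | N=90 |
|---|---|---|---|
| 5% (accepted) | 3.4 | 4.2 | 4.5 |
| 9% (cut-off) | 6.0 | 7.4 | 8.1 |
| 15% (rejected) | 10.1 | 12.5 | 13.5 |

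At 5% with N=90, the 5th to 95th percentile of the event count is 1 to 8.

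**Most events compatible with success.** Under IX.1 it is 5 of 67. Under the IX.3 rule with 90 evaluable patients:
- Clopper-Pearson: 6 events give an upper limit of 13.9%, 7 give 15.4%, so at most 6.
- Wilson: 7 events give 15.2%, so at most 6.
- Wald: 8/90 = 0.0889; 0.0889 + 1.96·√(0.0889·0.9111/90) = 14.8%, so at most 8.

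Section VI.5.3 lowers the count further, because patients are followed for vital status only after a recurrence.

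**Events per covariate.** Three covariates: 4.5/3 = 1.5 to 8/3 = 2.7. Five covariates: 4.5/5 = 0.9 to 8/5 = 1.6.

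**Simulation.** The covariate set is assumed, because the protocol gives none: N=90, a fixed number of events, 8 candidates (4 continuous; 4 binary with prevalence 50%, 30%, 30%, 20%), one continuous factor with true odds ratio 1.8 per SD, 700 datasets per cell. Screening used Mann-Whitney or Fisher at p<0.20 or p<0.05. Separation was tested by linear programming. The ratio is the mean estimated log odds ratio of the true factor divided by ln 1.8. For maximum likelihood (ML) it covers non-separated fits that contain the factor; for Firth, all fits that contain it.

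| Events | Model | Separated, of models fitted | ML ratio | Firth ratio |
|---|---|---|---|---|
| 4 | screened p<0.20 | 20% | 2.17 | 1.72 |
| 4 | screened p<0.05 | 12% | 2.73 | 2.29 |
| 4 | 3 / 5 fixed covariates | 34% / 58% | 1.25 / 1.46 | 0.96 / 0.99 |
| 5 | screened p<0.20 | 18% | 1.84 | 1.57 |
| 5 | screened p<0.05 | 6% | 2.35 | 2.06 |
| 5 | 3 / 5 fixed covariates | 23% / 51% | 1.22 / 1.23 | 0.98 / 0.99 |
| 8 | screened p<0.20 | 15% | 1.54 | 1.38 |
| 8 | screened p<0.05 | 5% | 1.79 | 1.65 |
| 8 | 3 / 5 fixed covariates | 5% / 22% | 1.08 / 1.06 | 0.97 / 0.90 |
| 13 | screened p<0.20 | 8% | 1.35 | 1.25 |
| 13 | screened p<0.05 | 3% | 1.53 | 1.43 |

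On the odds-ratio scale, a true 1.8 would be reported on (geometric) average as between 1.8^1.54 ≈ 2.5 and 1.8^2.73 ≈ 5.0 at 4 to 8 events. At p<0.05, no covariate was selected in 1 − 350/700 = 50% (8 events) to 1 − 250/700 = 64% (4 events) of datasets.

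**Why screening lowers separation.** For an unrelated binary factor of prevalence q and d events, the chance that all events fall in one level is q^d + (1−q)^d. With q=0.3 and d=4 this is 0.0081 + 0.2401 = 0.248. Nearly all of it is the unremarkable pattern of every event in the commoner level, which a univariate test does not retain.

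**The case against.** **Separation.** A reader might infer that the planned model will usually break down with infinite odds ratios. The stated procedure does not support that. With screening, about 5-20% of fitted models separate at 4 to 8 events. The high figures belong to models with three to five covariates forced in without screening: 23-58% at 4 to 5 events, and 5-22% at 8. Clinical relevance is also a selection criterion in IX.3, so some forcing-in is possible, but how much is not stated. This part of the objection stands.

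**The event count is an inference.** IX.1 expects a profile equivalent to other techniques and cites brachytherapy rates of 10-20% for soft-tissue ulceration and 5-10% for bone necrosis. Those rates are not restricted to grade ≥3, but they make 4 to 8 events a scenario rather than a stated expectation. At 13 events screened separation is only 3-8%. Overstatement remains, at 1.35 to 1.53 times.

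**The analysis plan can settle the details.** The estimator, a covariate cap and a sparse-event fallback could all be set there without contradicting IX.3, since Firth penalisation is still logistic regression. That is fair. What the protocol itself fixes is selection on univariate results, and that is the main source of bias: Firth after screening still overstates 1.38 to 2.29 times at 4 to 8 events.

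**The trial is called exploratory.** IX.2 says so to justify not adjusting systematically for multiplicity. This lowers the weight of the results but does not remove the bias.

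**Consequences.** A reader might infer that false predictors would feed into later dose-volume constraints. Nothing in the protocol says that they would.

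**Conclusion.** The point holds for selection. Following IX.3 as written, on the event numbers implied by IX.1, gives retained log odds ratios averaging about 1.5 to 2.7 times the truth at 4 to 8 events. Separation is a lesser, secondary risk.

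The event range rests on the protocol's 5% rate, 90 patients and the success rules. The size of the bias rests on the assumed 8 candidates, odds ratio of 1.8 per SD, prevalences and p-value thresholds. The simulated screen used p-values alone, without the clinical-relevance criterion. The direction of the bias was the same in every screened scenario tested; its exact size is illustrative.

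The matter deserves a change but is not critical. It touches one secondary, exploratory objective. The primary estimate, its confidence interval and the trial's conclusion are unaffected.

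**What to change.** In IX.3, and in the analysis plan due before database freeze:

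- Remove selection of covariates on univariate results.
- Name one or two predictors in advance, chosen by the sponsor from the clinical and planning data already collected.
- Fit them by Firth-penalised logistic regression with profile-penalised confidence intervals, and label the result exploratory.
- Describe all other factors by toxicity status, without modelling or selection.

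In the simulations, Firth with a prespecified set of three or five covariates gave 0.90 to 0.99 times the true log odds ratio at 4 to 8 events. A single prespecified predictor gave about 1.0 to 1.1 times. Penalisation alone is not enough: the screening step has to go as well.

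The cost is a change of wording, with no extra data or patients. The downside is that fewer factors are tested.
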